## 138 **4. STUDY DESIGN**

139 This study will use an individually randomised, single-blinded, controlled trial design. Prospective  
140 Australian overseas travellers will be recruited through a consumer panel provider to participate in  
141 the trial.

142 Participation in the trial will involve three steps, plus an optional follow up. Participants will first  
143 complete an initial (pre-intervention) survey (Step 1). They will then be randomly assigned to either  
144 the intervention or control group and receive a link to the corresponding materials based on their  
145 group assignment. Participants will be instructed to keep the REDCap survey open in a separate  
146 browser tab while reviewing the assigned materials (Step 2). After reviewing the materials, they will  
147 return to the REDCap browser to complete a post-intervention survey (Step 3). Participants who  
148 complete Step 1 but do not commence Step 3 will be sent up to two invitational reminders via email  
149 between 48-72hrs after completion of Step 1. Additionally, participants will be asked to consent to  
150 be contacted 3-6 months after the initial survey to complete an optional follow-up survey. This  
151 follow-up will investigate whether they undertook travel and received JE vaccine. Participants may  
152 opt out of this follow-up contact if they choose.

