### 5.1.1. SELECTION CRITERIA

In order to be considered eligible to participate in this study, participants must be:

- Age 18 years or older
- Currently living in Australia
- Able to read and understand English
- Planning travel to a JE-endemic region within the next 6-months

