### 5.3. DETAILS OF PARTICIPANT INVOLVEMENT

Participation in the trial involves three steps, all completed in a single web-based session (Figure 1):

- Step 1: Pre-intervention survey (approximately 7-10 minutes): all participants will complete the same survey
- Step 2: Review of assigned information (approximately 15 minutes): participants will be randomised to review either the JEVaDA tool (intervention) or the Healthdirect JE page (control)

Figure 1: Flowchart of Participant Involvement

[figure not shown]

- Step 3: Post-intervention survey (approximately 5 minutes): all participants will complete the same survey

Participants who complete both the pre- and post-intervention surveys will be considered to have provided complete responses. The total estimated time commitment is up to 30 minutes.

Participants will also be asked to consent to a follow-up contact 3-6 months after the initial survey for an optional follow-up survey. This follow-up will assess whether they travelled and received the JE vaccine. Participants can choose to opt out of this follow-up contact. Those who do not opt out will be asked to complete a brief (5 minute) follow-up survey 3-6-months post-intervention.

Since this trial is conducted online, participants must have access to an internet connection in order to participate.

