## **5.8. DATA COLLECTION**

All data will be collected via online surveys using REDCap (Research Electronic Data Capture), a secure, web-based application designed to support data capture for research studies. The surveys (Appendix 10) will gather information on participants' demographics, travel history, general health, health literacy, and JE vaccination history. Additionally, we will assess decisional conflict, knowledge, intention to vaccinate, and vaccine confidence as previously outlined. Questions from the WHO's Behavioural and Social Drivers (BeSD) survey will also be included to evaluate behavioural and social factors influencing vaccination decisions. Furthermore, self-reported JE vaccine uptake data will be collected through an opt-out follow-up survey administered 6 months post-intervention.

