## 10. APPENDIX 4: COMBINED SURVEY QUESTIONNAIRE (PRE-INTERVENTION, POST-INTERVENTION, FOLLOW-UP)

### JE Decision Aid RCT Pre-intervention Survey

## Questionnaire

### (Screening): Travel intentions

**These first questions are to find out if you're eligible for the study.**

Japanese encephalitis (JE) is a risk in 24 countries, shown on the map and listed below.

*NB: include a graphic of at-risk countries e.g. shaded map and country list*

Are you planning to spend time in any of these countries (outside of Australia) in the next six (6) months? Only include countries where you're planning to leave the airport.

|     |                   |
|-----|-------------------|
| Yes | [continue survey] |
| No  | [screen out]      |

**If Yes:** Please select the country where you plan to spend the most time from the drop-down list. If you will be spending equal time in more than one country, choose the country you will visit first. (required)

*NB: drop-down menu limited to JE-endemic areas excluding Australia*

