### 665 Travel experiences

666

667 **You mentioned you'll be visiting a JE-risk area in the next 6 months. We'd now like to ask you**  
668 **some questions about your planned trip.**

669

670 How many countries do you plan to visit during this trip?

- 671 ☐ 1  
672 ☐ 2  
673 ☐ 3 or more

674

675 **If one:** Which country are you planning to visit during your upcoming trip? (Drop-down list – i.e.  
676 must select one only)

677 **If two:** What is the first country you are planning to visit during your upcoming trip? (Drop-down list)

678 **If two:** What is the second country you are planning to visit during your upcoming trip? (Drop-down  
679 list)

680 **If three:** What is the third country you are planning to visit during your upcoming trip? (Drop-down  
681 list)

682

683 When are you planning to start your trip?

- 684 ☐ November, 2024  
685 ☐ December, 2024  
686 ☐ January, 2025  
687 ☐ February, 2025  
688 ☐ March, 2025  
689 ☐ April, 2025  
690 ☐ May, 2025

691

692 How long do you plan to travel for?

- 693 ☐ less than one month  
694 ☐ 1 month or more

695

696 Where do you plan to spend the most time during your trip?

- 697 ☐ More than half my time in cities  
698 ☐ More than half my time in rural areas (areas with a lot of farms or forests)  
699 ☐ About the same amount of time in both cities and rural areas  
700 ☐ Not sure

701

702 Are you planning to consult a healthcare provider for travel health advice for this trip?

- 703 ☐ Yes, I'm planning to  
704 ☐ Yes, I've already done so  
705 ☐ No, I'm not planning to  
706 ☐ Not sure

707

708 If yes, where do you plan to get travel health advice from? (select all that apply)

- 709 ☐ General practitioner / primary care  
710 ☐ Travel medicine clinic  
711 ☐ Pharmacist  
712 ☐ Internet  
713 ☐ Friend or relative  
714 ☐ Travel agent  
715 ☐ Other, please specify

716

717 **This set of questions asks about your past travel experiences.**

718

719 Have you ever travelled overseas (outside of Australia)?

- 720 ☐ Yes  
721 ☐ No → skip to "How many overseas trips..."

722

723 In what year was your last overseas trip? \_\_\_\_\_ (Dropdown box: 2014 or earlier to 2024)

724

725 How many overseas trips have you taken in your lifetime? (select one only)

- 726 ☐ 1 or 2  
727 ☐ 3 or 4  
728 ☐ Between 5 and 10  
729 ☐ More than 10  
730 ☐ None → skip next 4 questions

731

732 Which of the following regions have you visited in your lifetime? (select all that apply):

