| I am clear about which is more important to me (the benefits or the risks and side effects) |                |       |                            |          |                   |
| I have enough support from others to make a choice                                          |                |       |                            |          |                   |
| I am choosing without pressure from others                                                  |                |       |                            |          |                   |
| I have enough advice to make a choice                                                       |                |       |                            |          |                   |

|                                           |  |  |  |  |  |
|-------------------------------------------|--|--|--|--|--|
| I am clear about the best choice for me   |  |  |  |  |  |
| I feel sure about what to choose          |  |  |  |  |  |
| This decision is easy for me to make      |  |  |  |  |  |
| I feel I have made an informed choice     |  |  |  |  |  |
| My decision shows what is important to me |  |  |  |  |  |
| I expect to stick with my decision        |  |  |  |  |  |
| I am satisfied with my decision           |  |  |  |  |  |

966

967

1009 [Questionnaire](#)

---

1010

1011 In late 2024, you were planning a trip to a JE endemic area in [pipe previous answer]. Did you take  
1012 your trip as planned?

1013 - Yes – skip to ‘please select the country you spent the most time in from the drop-down list’

1014 - No

1015 How did your plans change?

1016 - Cancelled the trip

1017 - Chose a different destination

1018 - Delayed the trip

1019 - Other (please specify)

1020 Please provide any further details about why your travel plans changed (optional). *Free text box.* –

1021 **end survey**

1022 Please review this list of countries before answering the next question:

1023 ☐ Bangladesh

1024 ☐ Bhutan

1025 ☐ Brunei Darussalem

1026 ☐ Burma (Myanmar)

1027 ☐ Cambodia

1028 ☐ China

1029 ☐ India

1030 ☐ Indonesia

1031 ☐ Japan

1032 ☐ Lao People’s Democratic Republic

1033 ☐ Malaysia

1034 ☐ Nepal

1035 ☐ North Korea

1036 ☐ Pakistan

1037 ☐ Papua New Guinea

1038 ☐ Philippines

1039 ☐ Russia

1040 ☐ Singapore

1041 ☐ South Korea

1042 ☐ Sri Lanka

1043 ☐ Taiwan

1044 ☐ Thailand

1045 ☐ Timor-Leste

1046 ☐ Vietnam

1047

1048 Since November 2024, have you travelled to any of the countries listed above?

1049 ☐ Yes

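### The uptake follow-up may fall before an eligible trip starts (3-6 months in two sections, 6 months in a third), and a participant who has not yet left exits the survey before the vaccine question

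*Combined protocol and SAP*

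**What the plan says.** **Travel window.** Protocol section 5.1.1 admits people "Planning travel to a JE-endemic region within the next 6-months". The screening item in Appendix 4 matches it: "Are you planning to spend time in any of these countries (outside of Australia) in the next six (6) months". The baseline survey then asks "When are you planning to start your trip" and offers seven months, November 2024 to May 2025.

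**Follow-up timing.** Section 4 asks participants to agree to "be contacted 3-6 months after the initial survey to complete an optional follow-up survey". Section 5.3 has the same window: "Those who do not opt out will be asked to complete a brief (5 minute) follow-up survey 3-6-months post-intervention". Section 5.8 says uptake data are "collected through an opt-out follow-up survey administered 6 months post-intervention".

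**Follow-up questionnaire (Appendix 4).** The first question asks whether the trip was taken as planned, with yes and no as the only answers. No leads to "How did your plans change", where the choices are cancellation, a new destination, a delay, or other with text. An optional free-text box follows and the survey ends. The vaccine question comes later, on the route for people who travelled.

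**Analysis.** The SAP (Secondary Outcome 3) codes yes as 1, and no or not remembering as 0. SAP 2.2 assigns any missing data to multiple imputation. Neither mentions a trip that has not yet started.

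**The concern.** Two of the three timing statements allow contact up to 3 months before an eligible trip is due. For a participant in that position the instrument fails twice: an on-schedule trip is filed under changed plans, and the uptake item is never shown.

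Uptake is a named secondary outcome and part of the hypothesis in section 3.1. The participants lost are those with the longest lead time, who also had the longest to see a provider and be vaccinated. The analysed set would then lean towards short-lead travellers and be smaller than the number of respondents suggests. The SAP leaves open whether the empty values are missing data to impute or people outside the denominator.

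**Working it through.** **The plan's own figure.** The documents give no sample size, power or expected rate for uptake. Their only calculation is for the Decisional Conflict Scale (SAP 2.5), and it reproduces. With SD = sqrt(1 - 0.5^2) = 0.866, n per arm = 2 x [0.866 x (1.960 + 1.282) / 0.30]^2 = 175.1, against 175 stated; 350 / 0.70 = 500. It offers no margin for uptake.

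**Route of an on-schedule traveller contacted before departure.**
1. Trip taken as planned? Only no is truthful.
2. How plans changed? No listed change applies. Other, or the later text box, can reveal that the trip is still ahead.
3. The survey ends with no uptake value.

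The later question on travel since November 2024 does not help. As branched, yes at step 1 skips past it and no has already ended the survey. A no to that question would also end the survey.

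**Calendar check.** Assume enrolment in November 2024, inferred from the start-month list and from the follow-up wording about late 2024. A 3-month contact falls in February 2025, with March, April and May still ahead: 3 of 7 start options, or 4 of 7 if February trips have not begun.

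**Share not yet departed at contact month t.** The documents give no distribution of departures, so three patterns over 0 to 6 months are assumed:
- uniform: 1 - t/6
- front-loaded: (1 - t/6)^2
- back-loaded: 1 - (t/6)^2

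| Contact | Uniform | Front-loaded | Back-loaded |
|---|---|---|---|
| Month 3 | 50% | 25% | 75% |
| Month 4 | 33% | 11% | 56% |
| Month 5 | 17% | 3% | 31% |
| Month 6 | 0% | 0% | 0% |
| Spread evenly over months 3-6 | 25% | 8% | 42% |

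**Effect on precision if these cases are dropped.** The standard error is multiplied by 1/sqrt(1 - loss).
- Uniform, all at month 3: 1/sqrt(0.50) = 1.41, a rise of 41%.
- Uniform, spread over months 3-6: 1/sqrt(0.75) = 1.15, a rise of 15%.
- All at month 6: 1.00, no rise.
- Averaged front- and back-loaded patterns: 1/sqrt(0.917) = 1.04 and 1/sqrt(0.583) = 1.31.

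**Illustration in power.** Assume uptake of 10% versus 20%. If all 350 completers respond, power is 75% with no loss, 62% with 25% lost and 46% with 50% lost. If 70% respond, it is 59%, 47% and 34%. The rates and response levels are assumptions.

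**The case against.** The best reply is that section 5.8, the data collection section, already says 6 months. If that is the operating rule, almost every on-schedule trip has started by contact and the loss is close to 0%. This stands as a limit on size. It does not settle the matter, because sections 4 and 5.3 say otherwise. The timeline in section 5.12 does not decide it either: it shows data collection in month 3 only and ends at month 7, while the synopsis gives a duration of 1 year.

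A reader might infer three stronger things that the documents do not support.
- *That trips still to come cannot be told from cancelled ones.* The other option, the free text and the stored planned start month let an analyst identify many of them. What cannot be recovered is the uptake answer.
- *That the comparison between arms is biased.* Planned departure is recorded before randomisation, so loss driven by it should be similar in both arms. A different effect in longer-lead travellers would change whom the estimate describes. The documents give no figure from which to size such a shift.
- *That no re-contact exists.* None is stated in the visible text, but the participant flowchart and some pages around the follow-up questionnaire are not in the file.

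Imputation might recover some information, so the standard-error figures apply only if the cases are dropped. The SAP names no imputation model for uptake and does not say whether these people belong in it. It is also fair that uptake is optional, self-reported, secondary and unpowered.

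**Conclusion.** The concern holds as a timing conflict between sections 4 and 5.3 and section 5.8, together with a survey route that has no place for a trip still to come. The branching defect needs no assumption; its size does. With uniform departures, between 0% (contact at month 6) and 50% (contact at month 3) of on-schedule trips would have no uptake value, and the standard error rises by 0% to 41% if they are dropped. Reading the point as a certain loss of half the uptake data goes too far, because that needs contact at a flat 3 months, which no section prescribes.

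The consequence is lower precision and an estimate weighted towards short-lead travellers. Decisional conflict, knowledge and intention are measured in the enrolment session and are untouched. The point deserves correction, but it does not threaten the trial's main conclusion.

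**What to change.** 1. State one timing in sections 4, 5.3 and 5.8: contact at 6 months for everyone. This fits all three present statements and the 3-6 month contact that participants are asked to accept. Add the follow-up to the timeline: 6 months after data collection in month 3 is about month 9, past the table's end but within the 1-year duration.
2. Add an answer to the first follow-up question for a trip that is still to come. Route it to an item on whether a JE vaccine has already been received and, where consent allows, to a re-contact after departure.
3. Use the stored planned start month to separate trips not yet due from changed plans. State in the SAP whether trips not yet taken are in the uptake denominator and whether their values are imputed. If the follow-up has already been run, this step is still possible by comparing planned start month with contact date.

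**Cost.** Protocol and SAP wording, one answer option and its routing. Uptake data arrive up to 3 months later than with a 3-month contact, with somewhat more attrition and recall error. Timing each contact to the month after the planned start looks attractive, but it would reach November and December travellers at roughly 1-2 months and May travellers at about month 7, outside the agreed window. Any contact beyond 6 months, including a late re-contact, needs a change to the consent wording and an ethics amendment.

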#### **5.4. CONSENT AND WITHDRAWAL**

Potential participants will be directed to an online REDCap survey via a Monash-hosted URL. The landing page will provide a brief overview of the study (see Appendix 4 for the landing page script) and a link to a PDF of the full Participant Explanatory Statement (Appendix 5).

Participants will see a consent statement that reads: “By clicking the link below, you consent to participate in this study”. They will then have the option to click an “I Agree” button to begin the survey. Completion of the survey will imply consent to participate and permission to use the data collected for research purposes. Participants who decide not to take part may exit the survey at any time without any consequences.

#### **5.5. REIMBURSEMENT / INCENTIVES**

The ORU incentivises survey completion using a point-cash system. Respondents earn points for completing surveys, with 1-point equating to \$1. The number of points awarded is based on the length of the survey (i.e. the time spent completing it). The specific number of points awarded for this study will be determined by the ORU in accordance with their policies.

#### **5.6. RISKS TO PARTICIPANTS**

The anticipated risks to participants are minimal. Survey questions do not relate to sensitive topics. The survey will collect general demographic information, such as age, sex and place of residence (see Appendix 5: Pre-intervention survey – About you, p24). While this information might be categorised, it is not directly identifiable and is unlikely to lead to re-identification of individuals. Identifying details, such as names or dates of birth, are collected by ORU but will not be shared with study investigators and will not be part of the study data.

All survey data will be collected and managed within the REDCap database and stored in a secure, password-protected folder in password-protected electronic files on a secure Monash University Drive, accessible only to the core investigator team.

## 5.7. OUTCOME MEASURES

### 5.7.1. PRIMARY OUTCOME

The Decisional Conflict Scale (DCS) will be used to measure decisional conflict. The DCS is a well-established tool in decision-making research and is frequently employed in studies evaluating the effect of patient decision aids.(19) We will use the traditional 16-item version of the DCS, which is psychometrically validated and assesses five dimensions of decision making. This version employs a statement format, which has been extensively tested and is the most commonly used version in the literature.

The DCS includes 16 statements, each rated on a 5-point Likert Scale with each response giving a point value: 0 = 'strongly agree', 1= 'agree'; 2 = 'neither agree nor disagree'; 3 = 'disagree'; 4 = 'strongly disagree'. Scores for each items are summed, divided by 16 and then multiplied by 25 to yield a total score ranging from 0 (indicating no decisional conflict) to 100 (indicating extremely high decisional conflict). Scores below 25 are typically associated with decision implementation, which scores above 37.5 are associated with delaying decisions or feeling unsure about decision-making.(20) Sub scores can be calculated across five dimensions (informed, values clarity, support, uncertainty and effective decision). The DCS exhibits good test-retest reliability and internal consistency, and correlates well with knowledge and decision discontinuance. It is responsive to change and discriminates between individuals who make decisions and those who delay.

While DCS scores may be sensitive to timing, there is no consensus on the optimal timing of measurement. Most decision aid studies assess DCS immediately or shortly after the intervention.(19) In this study, we will measure DCS scores immediately before and after the intervention to minimise confounding factors, such as seeking additional information, and to address follow-up attrition issues observed in previous vaccine decision aid studies that measured DCS scores 1 or 2 weeks post-intervention.(21, 22) The primary outcome will be the change in decisional conflict, as measured by the DCS, at an individual level for all participants, from pre- to post-intervention. The outcome will be assessed as the difference in the change in DCS scores (post- vs. pre-intervention) between the intervention group (who receive the decision aid) and the control group (who receive standard information).

### 5.7.2. SECONDARY OUTCOMES

#### Knowledge

Knowledge of JE will be assessed at the individual level by comparing participants' responses to 9 knowledge statements about JE in the pre- and post-intervention surveys. Participants will be asked to indicate whether they believe each statement true, false or if they are not sure. Responses will be categorised as correct (where participants correctly identify a true statement as true or a false statement as false), incorrect (where participants incorrectly identify a true statement as false or a false statement as true), or "not sure" responses. The secondary outcome will be the change in the proportion of correct responses from pre- to post-intervention, with the difference in knowledge gains compared between the intervention and control groups.

Similar to other decision aid evaluation studies,(21-23) these knowledge questions have been developed specifically for this study, based on the content presented in the decision aid, and

knowledge considered important in the literature. The statements have been reviewed and refined with input from both clinicians and consumers to ensure accuracy and relevance.

